## Abstract

**Background:**

There is ample evidence from observational prospective studies that maternal depression or anxiety during pregnancy is a risk factor for adverse psychosocial outcomes in the offspring. However, to date no previous study has demonstrated that treatment of depressive or anxious symptoms in pregnancy actually could prevent psychosocial problems in children. Preventing psychosocial problems in children will eventually bring down the huge public health burden of mental disease. The main objective of this study is to assess the effects of cognitive behavioural therapy in pregnant women with symptoms of anxiety or depression on the child's development as well as behavioural and emotional problems. In addition, we aim to study its effects on the child's development, maternal mental health, and neonatal outcomes, as well as the cost-effectiveness of cognitive behavioural therapy relative to usual care.

**Methods/design:**

We will include 300 women with at least moderate levels of anxiety or depression at the end of the first trimester of pregnancy. By including 300 women we will be able to demonstrate effect sizes of 0.35 or over on the total problems scale of the child behavioural checklist 1.5-5 with alpha 5% and power (1-beta) 80%.

Women in the intervention arm are offered 10-14 individual cognitive behavioural therapy sessions, 6-10 sessions during pregnancy and 4-8 sessions after delivery (once a week). Women in the control group receive care as usual.

Primary outcome is behavioural/emotional problems at 1.5 years of age as assessed by the total problems scale of the child behaviour checklist 1.5 - 5 years.

Secondary outcomes will be mental, psychomotor and behavioural development of the child at age 18 months according to the Bayley scales, maternal anxiety and depression during pregnancy and postpartum, and neonatal outcomes such as birth weight, gestational age and Apgar score, health care consumption and general health status (economic evaluation).

**Trial Registration:**

Netherlands Trial Register (NTR): NTR2242

## Background

The burden of mental disorders is huge and at least comparable to the burden caused by many severe physical diseases. In the WHO Global Burden of Disease project it was estimated that 50% of all daily adjusted life years (DALY's) in the 15-44 years old are due to nine psychiatry-related conditions [1]. Depressive disorders are projected to rank second on a list of 15 major diseases in terms of burden of disease in 2030 [2]. In addition, a substantial part of the costs are caused by new cases, which accounts for 39.2% of the costs at population level [3]. Therefore, prevention of mental disorders is essential.

Maternal anxiety or depression during pregnancy is an important and potentially modifiable risk factor for cognitive, behavioural and emotional problems in her children [4-8]. Around 10-20% of all women are suffering from depression or anxiety during pregnancy [9-12]. The magnitude of the effects of maternal anxiety or depression on the child's psychosocial problems is considerable: it is estimated that up to 22% of the variance in behavioural problems is linked with prenatal anxiety, stress or depression [6]. The adverse effects seem to be lasting. For example, antenatal anxiety of the mother was related to behavioural or emotional problems of 4 year old children, independent of the mother's postnatal depression or anxiety [4], and higher anxiety levels of the mothers early in pregnancy were related to an increase in ADHD and other externalizing problems in their 8-9 year old children [13].

There are several ways in which depression or anxiety during pregnancy could have an adverse effect on the offspring. These ways can be divided in direct and indirect ways.

In the direct way, depression activates the maternal stress system leading to elevated cortisol levels, which might influence the development of the foetus' brain by passing the placenta.

An indirect adverse effect might be another mechanism, because women who suffer from antenatal depression have the tendency to take less good care of themselves (e.g. neglecting personal hygiene, sleeping problems, disturbed drinking and smoking habits, denying prenatal care). These consequences might all influence the development of the foetus [14-17].

Another indirect way in which depression might influence the offspring is when the antenatal depression remains after delivery and turns into a postnatal depression. In this way, mother-child attachment might be endangered, because the mother has a reduced ability to respond to the child. Children from depressed mothers have a higher risk on insecure attachment, which in turn is associated with cognitive, behavioural and emotional problems [1,18-20].

Finally, the association between antenatal depression and adverse outcomes in the offspring might be explained by genetic predisposition in both mother and child.

The effectiveness of psychological therapy in the treatment of both anxiety and depression has been shown in the past 50 years, especially for cognitive behavioural therapy (CBT) [21-25]. Although guidelines state that medication is an alternative effective treatment, the safety of antidepressants during pregnancy remains insecure [26].

Still, it is too early to implement CBT for depressed or anxious women to prevent psychosocial problems in the offspring. This is because in the development of such a preventive strategy, demonstration of the causality and size of the effect of the reduction of symptoms of depression and anxiety on child outcomes is a crucial step, a step that has not been taken to date. This knowledge gap will be filled by the results of the present experimental study.

Whatever the actual mechanisms involved are, there is presently convincing evidence that children whose mothers suffered from anxiety or depression during pregnancy constitute a high risk group for behavioural and emotional problems. On population level, substantial total mental health gains may be accomplished when depressed or anxious women are adequately treated during their pregnancy, even if the effect size of the treatment is relatively small.

We will perform a randomized controlled trial (RCT) in pregnant women with symptoms of depression or anxiety to study the effect of CBT as compared to care as usual (CAU) on the offspring's behavioural and emotional problems.

In the CBT arm, we expect more beneficial neonatal outcomes, in particular higher birth weight and less prematurity, which are risk factors for adverse cognitive and behavioural outcomes themselves [8]. We also anticipate reduced smoking and less drinking, with many physical and mental health benefits for the child as a result [17]. Since prenatal depression has shown to be related to postnatal depression, we hypothesize that our intervention will also counter postnatal depression, which in turn will benefit the mother - child attachment [27].

Finally, but not unimportantly, the reduction of symptoms of anxiety or depression during pregnancy and the early postnatal period is valuable in itself. It may further provide for a safer approach to reducing symptoms in pregnancy than antidepressant medication [15]

To date, no such study has been performed.

## Methods/Design

### Objective

The aim of this study is to examine the effect of cognitive behavioural therapy (CBT) in women with at least moderate symptoms of anxiety and/or depression at the end of the first trimester of pregnancy, on the extent of total behavioural and emotional problems in their children at 1.5 years of age, as compared with care as usual (CAU).

### Setting & Design

The source population will consist of all pregnant women in the Netherlands in the first trimester of their pregnancy. Women are recruited in obstetric care. In addition, we will invite pregnant women through advertisements in regional and national media targeted at pregnant women.

Women will be screened on anxiety and depression symptoms. Women with at least moderate symptoms of anxiety and/or depression at the end of the first trimester of pregnancy are either randomized to the intervention group in which they receive 10-14 sessions of CBT, or to the control group in which they receive care as usual.

Figure 1 shows the exact design of the study.

**Figure 1 F1:**
[figure not shown]
**Flow diagram**.

### Study outcome measures

The primary outcome in this project is the total emotional and behavioural problems score of the child according to the Child Behaviour Check List 1.5 - 5 (CBCL 1.5-5) at 18 months of age.

Secondary outcomes are the child's mental and psychomotor development at 18 months of age, the change in depressive and anxious symptoms in the mother, obstetric variables such as birth weight, gestational age and Apgar score, the socio-demographic and lifestyle factors, such as alcohol use, smoking and education, and cost-effectiveness of the therapy.

### Sample size

Studies on the prevention of mental disorders tend to suffer from problems of insufficient statistical power [28]. In the current study we aim to get around this problem by using a continuous primary outcome measure and by including a high risk group (selective prevention).

We decided that effect sizes of 0.35 (midpoint of small - medium effect size) or over on the total problems scale of CBCL 1.5-5 are to be detected. With alpha 5% and power (1-beta) 80%, we have to include 260 participants in our analyses. To account for some drop out we aim at 300 women entering the trial. If 50% eventually meets all criteria and gives informed consent, 600 screen-positives must be identified. The 50% rate is based on studies with psychological interventions during pregnancy aimed at reducing the occurrence of postnatal depression [27]. Given the figures in the literature [11,29] we can expect around 10% screen-positives on either the anxiety or depression screener. With an estimated 50% comorbidity between anxiety and depression this means that approximately 15% will be eligible for the randomisation. Therefore, 4000 need to be screened. Assuming a response rate of 75% [30] this implies that 5333 must be offered screening. To be on the safe side, we aim at screening 6000 women. If necessary for the recruitment of 300 women, the total number of screens may be increased.

### Inclusion

Women in obstetric care in the Netherlands with a significant level of anxiety (6 item STAI > = 42) or at least moderate depressive symptoms (EPDS > = 12) in their first trimester are invited to participate in the trial.

### Exclusion

Women fulfilling one or more of the following criteria will be excluded from participation:

1. Multiple pregnancy. We decided to exclude women with multiple pregnancy as they have a markedly increased obstetric risk; inclusion will threaten the homogeneity of the study population and thereby decrease the sensitivity to detect effects.

2. High suicidal risk according to the suicidality subscale score on the MINI International Neuropsychiatric Interview (MINI, defined as a positive response on the question on concrete suicide plans)

3. Presently receiving psychotherapy

4. Substantial physical disease or illegal substance abuse

5. No mastery of the Dutch language

6. Having a psychiatric history on bipolar disorder, psychoses and manic disorder

7. History of in vitro fertilization

### Assessments

Women will be asked to fill in questionnaires until their child is 1.5 years. This will be done at 8 occasions: the screener at baseline (T0), the additional baseline information (T1), and follow-up questionnaires at 24 and 36 weeks of gestation (T3 and T4), at 6 weeks postpartum (T5), 6 months postpartum (T6), 12 months postpartum (T7) and 18 months postpartum (T8).

At all time points, levels of anxiety and depression are monitored by the 6-item State Trait Anxiety Inventory (STAI) and the Edinburgh Postnatal Depression Scale (EPDS). As to be found in table 1, all other questionnaires can be filled in once or at several time points.

**Table 1 T1:** Assessments per measurement

	T0	T1	T2	T3	T4	T5	T6	T7
**Depression (EPDS)**	X	X	X	X	X	X	X	X

**Anxiety (STAI)**	X	X	X	X	X	X	X	X

**Personality NEO-FFI**		X		X		X		

**Life events before pregnancy (NLEQ)**		X						

**Life events during pregnancy**		X		X		X		

**Perceived social support (SSQ)**		X						

**Coping styles (UCL)**		X	X	X	X			

**Attitudes (DAS)**		X	X	X	X			

**Maternal attachment (ECR)**		X					X	

**Quality of life (EQ-5D)**		X	X	X	X	X	X	

**Sociodemographic & -economic factors**		X						

**Lifestyle**		X		X		X		

**Breastfeeding**						X		

**General health**		X						

**Health care consumption**		X			X	X	X	

**Previous pregnancies**		X						

**Suicidality (MINI)**		X						

**Clinical Diagnostic Interview (SCID-II)**		X						

**Child Behaviour (CBCL)**								X

**Child development (BSID-II)**								X

For anxiety, we use the Dutch version of the 6-item STAI. This self report questionnaire is as valid as the full 20-item version and has frequently been used to measure antenatal anxiety [29]. For the screening on depression we use the EPDS, which has 10 items [31]. This is the most frequently used self report depression screener in the postnatal period as well as during pregnancy and has been found particularly valid during pregnancy because this scale omits somatic symptoms [30].

The following information will be obtained from participants. The exact time of administration can be found in table 1.

• Life events before pregnancy will be assessed at baseline, using the Negative Life Events Questionnaire [NLEQ, [32]].

• Perceived social support will be measured according to the 9-item Social Support Questionnaire (SSQ)-short form [33].

• General health, socioeconomic position, ethnicity, smoking behavior, alcohol use, psychiatric history (whether the participant has had depression and/or anxiety symptoms before, whether she was treated for this and whether she is presently in treatment for these symptoms) will be assessed. Socioeconomic position will be assessed using five indicators: family income, educational level (father and mother), and occupational level (father and mother). This questionnaire is based on a questionnaire used in the Utrecht Health Project (Dutch acronym LRGP: Leidsche Rijn Gezondheids Project, http://www.zorggegevens.nl/zorg/eerstelijnszorg/leidsche-rijn-gezondheidsproject/). General health status will also be taken into account according to the EQ-5D [34].

• Personality will be assessed using the NEO Five Factor Inventory (NEO-FFI). The NEO-FFI is a shortened version of the NEO-PR-I [35] and covers the Big Five of personality (neuroticism, extraversion, openness, altruism and conscientiousness). These aspects each contain 6 subscales. The NEO-FFI contains 60 questions, 2 on each subscale. The present study will add 4 full subscales to the short version; two subscales of neuroticism, one of extraversion and one of conscientiousness. This is because we expect them to have the strongest association with persistence of depression and/or anxiety. The NEO-FFI is translated and validated in Dutch [36].

• Information on previous pregnancies, family size and composition, pregnancy related life events and on reactions on becoming a parent will be administered using questionnaires from the ALSPACstudy (http://www.bristol.ac.uk/alspac).

• Suicide risk will be measured using six screening questions from the MINI International Neuropsychiatric Interview [MINI, [37]].

• Maternal attachment style will be measured according to the ECR [38], which has been translated and validated for the Netherlands by Conradi et al. [39].

• Health care consumption will be assessed based on the TIC-P [40]. This instrument allows reliable recall over the past 6 months [41].

• Coping style will be assessed using the Utrechtse Coping Lijst, the UCL [42].

• A Dutch version of the Dysfunctional Attitude Scale (DAS) will be used to measure cognitions and attitudes [43].

• Obstetric variables such as gestational age, birth weight, Apgar score, complications such as (pre)eclampsia or HELLP, which will be obtained from midwifes. Women will be asked to give consent for this.

• Finally, we will use the SCID-I to screen for a possible clinical depressive or anxiety disorder [44]. The SCID-I is the only questionnaire used that has to be taken in a personal interview.

Besides questionnaires for the mother during her pregnancy and the first 1.5 years postpartum, there will be assessments in the child at 1.5 years of age.

One of the assessments is the Bayley Scale of Infant Development (BSID-II) [45]. This is a formal neuropsychological tool to assess the developmental level of a child between 1 and 42 months. It is individually administered by one of the researchers and consists of 3 subscales: cognitive development (mental development index), gross and fine motor development and the behavioural rating scale. This tool is widely used in both research and clinical settings and is considered the best and most applied method for the assessment of the child's development to date [46]. Importantly, the instrument has shown to be sensitive. In the context of our proposal, maternal anxiety in pregnancy explained as much as 11% of the variance in the Bayley scores in a study among two year old toddlers by LaPlante et al. [47].

The second assessment is the Child Behaviour Check List 1.5 - 5 (CBCL 1.5-5) including the Caregiver-Teacher Report form (C-TRF) and the Language Development Survey (LDS) [48]. This well established, reliable and valid scale designed for parents and caregivers comprises seven syndrome scales: emotionally reactive, anxious depressed, somatic complaints, withdrawn, sleep problems, attention problems and aggressive problems. In addition, it contains scales for internalizing, externalizing and total problems. Symptom scores may further be related to formal DSM-diagnostic criteria. The LDS provides a screen for delays in vocabulary and word combinations.

For the assessment of psychopathology in preschool children it is essential to obtain information from different sources [49]. Therefore we decided to include the C-TRF for the caregivers of the children other than their parents. Parents will be asked to hand these lists to the actual caregivers of their children, e.g. grandparents, baby-sitters, kindergarten-coaches, et cetera. Relevant in this respect, a review by Skovgaard [46] underlined the significance of both the developmental aspects (e.g. as measured with the BSID II) and the infant caregiver relation in the assessment of children 0-3 years of age.

The CBCL has been used successfully in several studies, amongst others on externalizing problems [50]. It has been translated and standardized for use in around 60 countries, including the Netherlands. The CBCL 1.5-5 is considered a sensitive instrument also deployed in current intervention studies [51,52]

Also, mother-child interaction will be measured by taping them for 15 minutes on video and scoring them afterwards on interaction points.

All assessors of both handling questionnaires filled in by the mother and measuring the children at age 1,5 are blinded for treatment assignment.

### Additional baseline data

Women agreeing to participate will be asked to provide additional baseline data at T1, as to find in table 1.

About half of these questionnaires are sent to the participants in print, the other half can be answered online. All follow-up questionnaires are available online.

After providing baseline data both in print and online, women are telephoned for the Structured Clinical Interview for DSM-II Disorders (SCID-VI). The SCID-II will allow us to study treatment effects additionally according to diagnostic categories rather than symptom levels.

### Randomisation

Right after the SCID-II interview, women are randomised 1:1 to either CBT or CAU.

We will create randomisation lists, stratified for parity and socio-economic position, with randomly permuted blocks of random size.

Women randomized to the CAU arm will be informed about being at risk of depression or anxiety disorder by the researchers and will be advised to contact their GP. A close record will be kept of all care provided in the CAU arm.

### CBT Intervention

The intervention consists of 10-14 individual sessions: 6-10 sessions during pregnancy and 4-8 sessions after delivery (once a week). The CBT will be conducted by registered psychologists, specialized in conducting CBT.

CBT posits that an individual's biased information processing leads to maladaptive feelings and behaviours which can culminate in psychological distress and eventually in psychiatric disorders. The main focus of the proposed intervention is targeted on identifying and changing dysfunctional cognitions and schemata (attitudes) specifically for pregnant depressed and anxious patients. In CBT, the Socratic dialog is used aiming to change these dysfunctional cognitions and attitudes permanently. CBT may therefore result in long term protection against psychosocial problems. It is therefore not surprising that cognitive therapy during the acute phase of depression also appears to be effective in reducing subsequent recurrence rates [25].

The first session will focus on the rationale CBT, i.e. the influence of (irrational or dysfunctional) cognitions and attitudes on feelings and behaviours. Additionally, goal setting will be initiated. These therapy goals will be unique for each patient. The subsequent sessions will be targeted at identifying and amending irrational cognitions and attitudes related to pregnancy, delivery, concerns about the (unborn) child and the future family situation. Each session will address specific pregnancy-related cognitions. Additionally, patients will be taught how dysfunctional cognitions and attitudes affect adversely feelings and behaviours.

These dysfunctional cognitions and attitudes will be challenged and replaced by functional cognitions and attitudes. After each session, patients will be given home work. For example, patients will be asked to register negative experiences, and accompanying cognitions, feelings and behaviours. Finally, in the last two to four sessions, the newly learned cognitions and attitudes will be consolidated.

### Data analysis

If necessary, skewed continuous variables will be transformed to normality prior to the analyses. The primary outcome, i.e. the CBCL scores at month 18, will be compared between the treatment arms using the unpaired t-test. This test will also be used for detecting differences in the Bayley scores by month 18 and the obstetric variables measured at birth. The latter group of variables will be tested using the Chi2 test if categorical. Differences in attachment style at month 12 will be analyzed using analysis of covariance with the baseline variable as a covariate. Continuous outcomes that were measured more than twice (e.g. EPDS and STAI) will be analyzed as dependent variables using linear mixed models for fixed and random effects. These models are superior for the analysis of longitudinally correlated data and can optimally deal with missing values [53]. A mixed model ascribes a unique intercept and slope estimate to each individual, while making use of information across individuals for predicting these quantities. In these analyses, a treatment*time variable indicating the effect of the intervention will be included as an independent variable. If despite randomisation important baseline differences exist in prognostically important variables such as the extent of social support or history of life events, they will be adjusted for. Additional analyses will be conducted to demonstrate mediation of the effect of CBT on the child's outcomes by maternal symptom level, alcohol or nicotine consumption in pregnancy, medication use or neonatal outcomes.

The analyses will primarily be carried out according to the intention-to-treat (ITT) principle, i.e. the participants will be analyzed according to their randomized allocation, regardless of the actual CBT undergone, or time in study after baseline. Aside from the optimal validity of ITT analyses, they quantify the effects on the outcome measures that would be obtained in practice. The magnitude of the effect measured in an ITT analysis incorporates the effects caused by non-adherence to CBT, behavioural changes, et cetera. Secondary analyses will be of the 'per protocol' type meaning that they will be restricted to those women that had all of the CBT sessions.

Considering specific target populations, there is evidence that the socio-economically deprived may have more benefit from treatment of depression during pregnancy [15]. Therefore, subgroup analyses will be undertaken according to socio-economic position. Subgroup analyses will also be undertaken according to parity.

Differences in effect of CBT between subgroups will be statistically evaluated by testing treatment by subgroup interaction terms. Effect parameters will be supplied with a 95% confidence interval.

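### The primary t-test leaves out the stratification factors and the baseline maternal scores, so it is slightly conservative and less precise than it could be

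*Protocol article*

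**What the plan says.** On allocation, the Randomisation section says that "women are randomised 1:1 to either CBT or CAU", using lists "stratified for parity and socio-economic position, with randomly permuted blocks of random size".

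On the primary comparison, the Data analysis section says: "The primary outcome, i.e. the CBCL scores at month 18, will be compared between the treatment arms using the unpaired t-test". The same test is named for the Bayley scores and the continuous birth outcomes. Parity and socio-economic position come back only as subgroup factors with interaction tests.

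The Data analysis section also has a conditional rule. If important baseline differences appear in prognostic variables despite randomisation, those variables will be adjusted for. Social support and life events are the examples given. For attachment style, by contrast, an analysis of covariance on the baseline value is planned outright.

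On size, the Sample size section targets "effect sizes of 0.35 (midpoint of small - medium effect size) or over on the total problems scale of CBCL 1.5-5". It continues: "With alpha 5% and power (1-beta) 80%, we have to include 260 participants in our analyses". On the prognostic role of maternal symptoms, the Background reports an estimate that "up to 22% of the variance in behavioural problems is linked with prenatal anxiety, stress or depression". Table 1 shows EPDS and STAI at T0 and T1. The Additional baseline data and Randomisation sections place T1 before allocation.

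**The concern.** Two separate things are left out of the primary model, and they have different consequences.

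- **The strata.** Blocking within strata keeps the arms balanced on parity and socio-economic position, so differences between strata contribute little to the true sampling variance of the treatment difference. The t-test still counts that between-stratum variance in its standard error. The interval then covers more often than 95% and the test rejects less often than 5% under the null.
- **Baseline EPDS and STAI.** They are not stratified on. Omitting them gives a correct 95% interval, but a wider one than the data allow if the scores predict the child's CBCL score.

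At stake is precision that the trial has already paid for. The sample size section opens by noting that prevention studies tend to lack power, and 260 analysed leaves almost no margin over 80%. The conditional rule also leaves the primary model to be settled after the baseline data have been seen.

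**Working it through.** **Inputs.** From the Sample size section: d = 0.35 (SD = 1), alpha 5%, power 80%, 260 analysed, 300 randomised (implied loss 1 - 260/300 = 13.3%). From the Randomisation section: 1:1 allocation. From the Background: up to 22% of variance. Every other R² below is an assumption, since the protocol gives none for this sample.

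**1. Reproduce the stated size.** The normal approximation gives n per arm = 2(1.96 + 0.84)²/0.35², about 128.1, rounded up to 129, or 258 in total. The noncentral t gives 129.1, so 130 per arm and 260 in total, which is the stated figure. Power at 130 per arm is 80.3%. A one-sided test would need 202 and does not reproduce the figure. The plan is therefore sized for a two-sided unadjusted t-test.

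**2. Strata only.** If the strata explain a share R² of the variance and are balanced, the true standard error is √(1 - R²) times the one that the t-test uses. The interval is then too wide by 1/√(1 - R²) - 1, and the type I error is 2·P(Z > 1.96/√(1 - R²)).

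| Assumed R² of strata | Interval too wide by | Type I error |
|---|---|---|
| 0 | 0% | 5.0% |
| 2% | 1.0% | 4.8% |
| 5% | 2.6% | 4.4% |
| 10% | 5.4% | 3.9% |

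The formula assumes perfect balance among those analysed. A simulation (4,000 runs, N = 260, six assumed strata, permuted blocks of 2, 4 or 6) at R² = 10% gave a type I error of 4.2%. Interval width was 0.488 SD for the t-test and 0.463 SD with strata in the model; power was 80.6% and 83.6%. A second simulation with 300 randomised and random dropout to 260 (12,000 runs) gave about 4.1%. About 4% is thus the low end of the assumed range.

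**3. Strata plus baseline scores.** Adjustment raises the effective effect size to 0.35/√(1 - R²). Power is at 130 per arm by noncentral t; the N for 80% power is by normal approximation.

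| Assumed total R² | Effective d | Power | Total N for 80% |
|---|---|---|---|
| 0 | 0.350 | 80.3% | 258 |
| 5% | 0.359 | 82.2% | 244 |
| 10% | 0.369 | 84.2% | 232 |
| 15% | 0.380 | 86.2% | 218 |
| 22% | 0.396 | 88.9% | 200 |

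**4. Cost if nothing is prognostic.** In simulation with R² = 0, power was 79.9% for the t-test and 79.6% with full adjustment, which is equal within simulation error.

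**5. Does the conditional rule fill the gap?** It acts on observed imbalance. Stratification is there to prevent imbalance in the strata, so the rule would seldom bring them in. For EPDS and STAI, the gain in precision comes from their link with the outcome and is there even when the arms are balanced.

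**The case against.** The best defence is that nothing is broken. The planned test is the one the sample size was computed for, it meets its target, and its error is on the safe side. The article says that it tackles low power in another way, through a continuous outcome and a high-risk group. All of that stands.

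The conditional rule has an open list of examples, so baseline symptoms could enter the model. It would be wrong to say that the plan ignores prognostic baseline variables in every case. The rule still does not fix the model in advance.

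The size of the gain is uncertain. Nothing in the article says how much CBCL variance parity or socio-economic position explains. At 1-2% the power gain is only 0.4-0.8 points. The 22% is an upper figure for anxiety, stress or depression in general, and entry requires STAI of at least 42 or EPDS of at least 12, which narrows the range of scores. A value below 22% is likely here.

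A condensed article may leave covariates to a fuller document. That carries limited weight, because this article names the primary test outright.

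A reader might infer that the mismatch makes the primary test invalid, inflates false positives or leaves the trial underpowered. The protocol's own figures do not support this: type I error is at or below 5%, and power at 260 is 80.3%. Nor does omitting EPDS and STAI make the interval wrong; only the omission of the strata makes it over-cover.

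**Conclusion.** The point holds as lost efficiency with slight conservatism. The stratified design and the unadjusted primary test do not match, and the adjust-if-imbalanced rule does not reconcile them.

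The size depends on an R² that the protocol does not supply. From the strata alone, assuming 0-10%, the effect is modest and possibly negligible. With maternal scores added, the gain runs from nothing at R² = 0 to about 9 power points at the 22% upper bound. The true value probably lies well inside that range. There is no baseline CBCL for the child, so maternal measures are the only baseline scores available.

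The change is worth making because its cost is negligible, not because the planned test fails.

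**What to change.** State the primary analysis as a linear model of the CBCL total problems score on treatment, with these prespecified covariates:

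- parity and socio-economic position, categorised as they were for randomisation;
- EPDS and STAI from T1, the last assessment before randomisation.

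Let this model replace the adjust-if-imbalanced rule for this outcome. Use the same model for the Bayley scores and the continuous birth outcomes, and keep the t-test as a sensitivity analysis.

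The cost is a sentence or two of wording and a few degrees of freedom. The covariates are already collected before allocation. Two details need a line each: how the five socio-economic indicators form the randomisation stratum, and a simple prespecified way to handle any missing baseline score. The sample size need not change.
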